### Study interventions

#### Mindfulness-Based Stress Reduction (MBSR) program

The MBSR program being offered in this study is modeled after the eight-week program developed and popularized by Jon Kabat-Zinn to reduce pain and stress [24]. The MBSR program is offered in a group setting wherein participants meet with trained facilitators once a week for two and a half hours each (except for the first class which is three hours) along with a four-hour retreat offered on a weekend (between weeks six and seven)—thus resulting in 24.5 h of face-to-face training. In these classes, facilitators cover a combination of experiential practices, didactics and teachings on the topics of mindfulness, and mindful movement exercises. These practices and teachings all center on cultivating present moment awareness in a framework that promotes acceptance and non-judgment. Moreover, the participants are provided with several opportunities to engage in small and large group-based discussions that offer a platform for social support, validation, and shared experiences. Supplementary Table 1 provides the agenda for each of the eight sessions of the MBSR program as well as the practices taught during the retreat. In addition to these classes, all participants are invited to engage in 30 min of formal homework practices, delivered through our web/mobile-based, in-house application that was named after the study—HealthyAgers. Working with a team of inter-disciplinary experts, including certified mindfulness experts, psychologists, wellness coaches, and computer programmers, we have carefully designed this iOS/Android mobile/web application to deliver and track guided meditation practices. This application will allow us to collect objective practice data on all our participants with the application providing information on minutes practiced, the frequency of engagement in mindfulness practices per week, and additional meta-data, including preferred practices, time of day preference, etc. After the eight weeks of the intervention, participants will be invited to continue engagement with mindfulness practices on their own, five times per week, for 12 months with two-hour, group-based booster sessions provided by the study facilitators every three months. Prior to the pandemic, all intervention sessions were provided in our group psychotherapy rooms housed in the Department of Psychology. Sessions shifted to the Zoom platform in March 2020 and continue to be offered virtually.

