**Discussion:**

This study will establish the efficacy of a group-based, low-cost mind–body intervention for the inter-related facets of attentional control and mind-wandering in older adults. Strengths of this study include a well-designed, placebo-controlled comparison group, use of web/mobile application to track study adherence, and longitudinal follow-up.

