### Setting

Assessments and the intervention will be conducted in the Psychology Building at The Ohio State University. The Department of Psychology houses individual neuropsychological testing rooms to allow for the convenient administration of neuropsychological and emotional regulation measures. All structural and functional MRI data will be collected at the Center for Cognitive and Behavioral Brain Imaging housed in the Department of Psychology at Ohio State. Prior to the onset of the COVID-19 pandemic, all intervention sessions were provided in the group therapy spaces housed in the Department of Psychology. These spaces were specifically designed for offering mindfulness and LifeEd sessions. Intervention sessions have been shifted to a virtual format following the COVID-19 pandemic, but assessment sessions continue to be collected in-person.

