### Study procedures

Participants are being drawn from the greater central Ohio area. Recruitment for the study started in August 2018 and is currently ongoing. We are implementing a multi-medium recruitment strategy, advertising for the study using both printed and online communications, in-person recruitment, community outreach, and other opportunities aimed at our targeted demographic. Table 1 provides a list of our primary recruitment sources for the study. Participants interested in the study will either complete a phone screen or an online survey that is designed to collect basic demographic information, current medications, and history of physical as well as psychological health. Participants who meet basic inclusionary criteria are then invited to the Clinical Neuroscience Laboratory at The Ohio State University to complete an in-person screening session. Those meeting the study criteria as described above are invited for additional behavioral and imaging-based assessments. Table 2 lists the measures administered at pre-training, post-training, and at 6-month and 12-month follow-up sessions. Participants are also given a Qualtrics link with the following survey measures at baseline, pre-training, post-training, and the two follow-up sessions: the Mindful Attention Awareness Scale [53], the Difficulties in Emotion Regulation Scale [54], the Perceived Stress Scale [55], the World Health Organization Quality of Life – BREF [56], the Beck Anxiety Inventory [57], the Five Facet Mindfulness Questionnaire [58], the Coronavirus Anxiety Scale [59], Psychological Stress Associated with the COVID-19 Crisis [60], and the Everyday Discrimination Scale [61].

**Table 1 Tab1:** List of primary recruitment sources being employed for the study

Category	Recruitment Strategy
**Printed Materials**	Flyers were displayed in recreational centers, community centers, libraries, cafes, barber shops, and churches throughout the central Ohio area
	Advertisements were displayed on Campus Area Bus Service buses at The Ohio State University
	Post cards were distributed to households in the central Ohio area
**Online Recruitment**	Research Match (an online recruitment tool with a database of participants.)
	Study Search (a database of active studies at The Ohio State University)
	Media advertisements (Facebook, Columbus Dispatch, Ohio State University’s OnCampus newspapers)
**Radio Advertisement**	Radio Stations aired an advertisement for the study (106.7 The Beat)

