### Randomization

Eligible and consenting participants will be randomized after completing baseline assessments to one of two groups: MBSR or LifeEd. A random permuted-block design (blocks of size 2 and 4) will be used, and the randomization with an allocation ration of 1:1 will be stratified by sex assigned at birth (male, female), cognitive status (cognitively normal, MCI), and MRI eligibility (eligible, not eligible) to ensure balance across these important factors. The biostatistician on the team, [name], prepared and maintains the randomization sequence for the eight strata. The project coordinator has been given concealed envelopes and only after a participant completes all pre-assessment sessions and is deemed eligible for the study does the project coordinator open the envelope from the respective stratum and assign the participant to either the MBSR or the LifeEd group. The project coordinator, the study facilitators and supervisors, and the study biostatistician will be the only members of the team who will be unblinded to group assignment. All personnel conducting assessments, behavioral or neuroimaging, will remain blind to group assignment.

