#### Lifestyle Education (LifeEd) program

The LifeEd program is an active control group against which we will compare the effects of the MBSR program. Participants are provided with psychoeducation on topics related to healthy living and wellness for older adults. The series includes didactics covering the latest evidence-based science on: sedentary behavior, physical activity, cognitively stimulating activities, social support, sleep, stress management, nutrition, and hydration. This program is designed to control the many active ingredients of a group-based psychotherapeutic program, like MBSR. As such, it is matched for setting (group), number and training of facilitators, amount of time receiving in-person instruction, and amount of assigned homework time. In addition, to ensure that it is matched with respect to engagement in experiential exercises, participants are introduced to light stretching and toning exercises during the two-and-a-half-hour class sessions. These stretching and toning exercises were designed by a certified yoga instructor with expertise in working with older adults. Supplementary Table 1 also provides detailed agendas for all eight sessions of the LifeEd program. Moreover, participants in the LifeEd program also have access to the web/mobile application—HealthyAgers—with participants in this group engaging in the following combination of homework practices: light stretching and toning exercises three times/week, reading two popular press articles and answering questions related to them once a week, and watching one to two videos and answering related questions once a week. All homework materials are standardized to take ~ 30 min with all readings and videos delivered through the in-house application. Finally, like the MBSR program, participants in the LifeEd group are also being provided booster sessions once every three months with the encouragement to continue completing homework practices five times per week. Prior to the pandemic this group also met in-person with trained facilitators and transitioned to Zoom sessions starting in March 2020 because of the COVID-19 pandemic.

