After preprocessing of behavioral and neuroimaging data, all data will first be tested for normality, outliers, and errors. We will then compute summary statistics and compare groups’ baseline demographic and clinical characteristics; although randomization should balance the groups with respect to these characteristics, with a finite sample size, there may be some residual imbalance. Particular attention will be paid to characteristics that may be associated with outcomes (e.g., education, depression scores) as chance imbalance in these characteristics may confound the intervention effects. All statistical analyses conducted as part of the trial will be intent-to-treat. The primary outcome variables for this study are indices of attentional control and mind-wandering. To examine the immediate effects of mindfulness training, we will use a linear mixed model to account for the within-subject correlation arising from measuring each subject at two timepoints. Group (MBSR, LifeEd), Time (pre and post-training), and the Group X Time interaction will be defined as fixed effects, with covariates, when applicable (e.g., those identified as randomly differing between groups) included as fixed effects. Each participant’s intercept will be included as a random effect. To determine the maintenance effects of mindfulness meditation, we will construct a separate mixed linear model examining the long-term efficacy of mindfulness meditation with Time (pre-training, 6-month follow-up, and 12-month follow-up), Group (MBSR, LifeEd), and the Group X Time interaction effects. Secondary factors of functional connectivity, fluid and everyday cognition, emotion dysregulation and inflammation will also be examined by constructing linear mixed models.

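### Both arms moved from in-person to Zoom delivery mid-trial, but neither stated model has a delivery-era term, so the effect is an average over two formats with some loss of precision

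*Protocol article*

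**What the plan says.** The protocol article reports the change of delivery openly and in several places.

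- **Recruitment (Study procedures):** "Recruitment for the study started in August 2018 and is currently ongoing".
- **Mindfulness arm (MBSR program):** "Sessions shifted to the Zoom platform in March 2020 and continue to be offered virtually".
- **Control arm (LifeEd program):** "Prior to the pandemic this group also met in-person with trained facilitators and transitioned to Zoom sessions starting in March 2020".
- **Assessments (Setting):** "Intervention sessions have been shifted to a virtual format following the COVID-19 pandemic, but assessment sessions continue to be collected in-person".
- **Allocation (Randomization):** "A random permuted-block design (blocks of size 2 and 4) will be used", with a 1:1 ratio, "stratified by sex assigned at birth (male, female), cognitive status (cognitively normal, MCI), and MRI eligibility (eligible, not eligible"). Era and delivery format are not stratification factors.
- **Immediate-effect model (Data management and analysis):** "Group (MBSR, LifeEd), Time (pre and post-training), and the Group X Time interaction will be defined as fixed effects". There is a random intercept per participant. Covariates enter as fixed effects where applicable, and the example given is variables found to differ between the groups by chance.
- **Maintenance model (same section):** the same structure, with Time at pre-training, 6 months and 12 months.
- **Conclusion (Abstract, Discussion):** "This study will establish the efficacy of a group-based, low-cost mind–body intervention".

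Neither model names a term for delivery format or calendar era. Study procedures lists coronavirus-anxiety and COVID-stress scales, but the analysis section gives them no role.

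**The concern.** The article was written after the switch, describes it, and then commits to models that take no account of it. Two things follow.

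1. **Interpretation.** If the MBSR-versus-LifeEd effect differs by format, the single Group x Time estimate is a weighted average, with weights set by how many people happened to enrol on each side of March 2020. A reader told that efficacy was established would not know which format the figure describes. The article itself gives a reason why format could matter: its main Discussion names social support and collaborative group discussion as non-specific influences on attention. The MBSR section still counts the training hours as face-to-face.

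2. **Precision.** If average change over time differed between eras in both arms alike, that difference goes into the residual unless era x Time is in the model.

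The covariate rule does not reliably repair this. Its example selects variables that differ between arms, and concurrent 1:1 allocation in small blocks should keep era close to balanced. Even if era did enter, covariates are described only as fixed effects. A main effect of era shifts a participant's level at both visits and does not absorb an era-specific change.

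**Working it through.** **Inputs from the article.** Switch in March 2020 in both arms; recruitment from August 2018; 1:1 blocks of 2 and 4 in eight strata; partial eta squared 0.088, alpha 0.05, N = 103 for power above 0.80; 25% drop-out; 150 planned. **Not given, hence assumed:** the share enrolled per era, any era shift in outcomes, any difference in effect by format, and the pre-post correlation.

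**1. The plan's own figure.** f² = 0.088/(1 − 0.088) = 0.0965, so f = 0.311. With a noncentral F, noncentrality f²N and 2 numerator degrees of freedom, N = 103 gives power 0.8004, which reproduces the stated figure. With 1 numerator degree of freedom the requirement is N = 84. The steps below use d = 2f = 0.621 as the yardstick for a two-arm contrast in change. On that basis (1 df, normal approximation) power at N = 103 is 0.88.

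**2. Is the contrast biased?** If a shift is common to both arms, the arms are exchangeable under the null and the expected difference is zero. A simulation agrees. Settings: eight equally likely strata, blocks of 2 and 4, half the sample after the switch, change score with SD 1; 3,000 runs at N = 150 under the null and 2,000 runs at N = 104 with d = 0.621.

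| Common era shift (SD of change) | Mean null estimate, no era term | Type I error, no era term | Power, no era term | Power, era term |
|---|---|---|---|---|
| 0.5 | 0.001 | 0.050 | 0.87 | 0.89 |
| 1.0 | 0.007 | 0.027 | 0.82 | 0.88 |

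The simulation standard error of the mean estimate is about (2/√150)/√3000 = 0.003. The era-adjusted estimate in the 1.0 SD row drifts similarly (0.005), so this is noise. There is no bias and no inflation of type I error. The cost is about 2 to 6 points of power.

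**3. Variance of change.** With unit variance at each visit and pre-post correlation ρ, the variance of change is 2(1 − ρ). Omitting an era-by-time difference δ, with a share p in one era, adds δ²p(1 − p).
- ρ = 0.5, δ = 0.3, p = 0.3: 0.09 × 0.21 = 0.0189, on 1.0, is +1.9%.
- ρ = 0.7, δ = 0.5, p = 0.5: 0.25 × 0.25 = 0.0625, on 0.6, is +10.4%.

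**4. The average if the effect differs by format.** Pooled d = (1 − w)d + w·r·d, where w is the Zoom share and r is the Zoom effect as a fraction of the in-person effect. Taking r = 0.5 purely as illustration:

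| Zoom share w | Pooled d | Power, N = 103 |
|---|---|---|
| 0.3 | 0.53 | 0.76 |
| 0.5 | 0.47 | 0.66 |
| 0.7 | 0.40 | 0.54 |

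**5. Can the trial tell the formats apart?** The standard error of the Group x Time x era contrast is √(4/n₁ + 4/n₂), against √(4/N) for the overall effect. At N = 103 with an even split: √(4/51.5 + 4/51.5) = 0.394, twice the overall 0.197. Power for an interaction of 0.621 is then Φ(0.621/0.394 − 1.96) = 0.35. At a 20/80 split the ratio is 2.5 and power is 0.24. At N = 112 (about 150 × 0.75) the range is 0.26 to 0.38.

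**6. Exposure of follow-up.** The 12-month visit falls about 14 months after baseline (eight weeks plus 12 months). If visits ran to schedule, baselines from about January 2019 onward led to a 12-month visit in or after March 2020. That is about 14 of the 19 pre-switch recruitment months (August 2018 to February 2020). Enrolment by month is not given, so this counts months, not participants.

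**The case against.** The strongest reply is that this is an omission from a condensed article. Format subgroups and pandemic-visit handling often sit in a full protocol or analysis plan, and neither is shown. That limits the point but does not remove it: the article does state its models and covariate rule, and as stated they make no provision for a change that it reports itself.

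Several stronger readings are tempting, and the document does not support them.

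- **That pooling biases the result.** It does not. Both arms switched in the same month under concurrent small-block randomization, so a common shift cancels in Group x Time. This also holds for follow-up, where pre-pandemic baselines paired with later visits occur in both arms.
- **That the trial tested two different programs.** The article describes one manualized program per arm, with the same session schedule, app-based homework, synchronous small groups and matched timing. Only the delivery medium is reported to change, and assessments stayed in person.
- **That the pandemic altered the outcomes.** Nothing in the article shows a change in attentional control or mind-wandering. Collecting COVID scales shows that pandemic stress is measured, not that task performance moved.
- **That era can never enter the model.** The covariate list is open and its rule is only an example. Era is not barred, but nothing written calls for it.

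It is also fair to say that an average over delivery conditions is a legitimate estimate, that no passage suggests different effects by format, and that the era contrast is too weak to settle the matter.

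**Conclusion.** The point holds as one of interpretation and modest precision, not of validity. Both arms changed delivery format during recruitment. Both stated models pool across the change, and the stated covariate rule would not reliably account for it. The Group x Time estimate is therefore an enrolment-weighted average over in-person and Zoom delivery.

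The size depends on assumptions that the document cannot settle. Era shifts in change of 0.3 to 0.5 SD add about 2% to 10% to the variance of change. Shifts of 0.5 to 1.0 SD of change cost about 2 to 6 points of power when half the sample is in each era. If the effect were halved on Zoom, pooled d would be 0.40 to 0.53 instead of 0.62; that is an illustration, not an expectation. The change is worth making because it is nearly free and fixes the handling of era before the outcome analysis.

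**What to change.** 1. **Immediate-effect model:** add delivery era (before or after March 2020, by the participant's class dates) and era x Time as fixed effects, whether or not era is balanced between arms.
2. **Maintenance model:** add a before/after March 2020 term by visit date, so that earlier baselines with later follow-up are modelled.
3. **Straddling participants:** state in advance how those whose classes or follow-up cross the switch are coded.
4. **Reporting:** give Group x Time by era and the Group x Time x era contrast as exploratory, with intervals and an explicit note of the low power.
5. **Conclusion:** word efficacy for the mixture of formats delivered, and report the number randomized in each era by arm.

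If a full protocol or analysis plan already does this, a sentence pointing to it is enough. The cost is analysis wording, one or two degrees of freedom per model, and an exploratory contrast too weak to support a separate claim about either format. The dates are already known, so no new data are needed.

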#### Lifestyle Education (LifeEd) program

The LifeEd program is an active control group against which we will compare the effects of the MBSR program. Participants are provided with psychoeducation on topics related to healthy living and wellness for older adults. The series includes didactics covering the latest evidence-based science on: sedentary behavior, physical activity, cognitively stimulating activities, social support, sleep, stress management, nutrition, and hydration. This program is designed to control the many active ingredients of a group-based psychotherapeutic program, like MBSR. As such, it is matched for setting (group), number and training of facilitators, amount of time receiving in-person instruction, and amount of assigned homework time. In addition, to ensure that it is matched with respect to engagement in experiential exercises, participants are introduced to light stretching and toning exercises during the two-and-a-half-hour class sessions. These stretching and toning exercises were designed by a certified yoga instructor with expertise in working with older adults. Supplementary Table 1 also provides detailed agendas for all eight sessions of the LifeEd program. Moreover, participants in the LifeEd program also have access to the web/mobile application—HealthyAgers—with participants in this group engaging in the following combination of homework practices: light stretching and toning exercises three times/week, reading two popular press articles and answering questions related to them once a week, and watching one to two videos and answering related questions once a week. All homework materials are standardized to take ~ 30 min with all readings and videos delivered through the in-house application. Finally, like the MBSR program, participants in the LifeEd group are also being provided booster sessions once every three months with the encouragement to continue completing homework practices five times per week. Prior to the pandemic this group also met in-person with trained facilitators and transitioned to Zoom sessions starting in March 2020 because of the COVID-19 pandemic.

**FORMAT OF DELIVERY**	
1. Rationale for MBI adaptations	1. MBSR and LifeEd materials adapted for older adults and include discussions around healthy living, barriers, challenges, and ideal outcomes
2. MBI and control group matching	2. MBSR and LifeEd sessions take place for 2.5 h (first session is for three hours), 1 × per week, for 8 weeks
3. Plan for implementation setbacks	3. Trained back-up facilitators for MBSR and control groups; scheduled website maintenance and back-up technicians for web failures
